## Abstract

**Background:**

Child health, nutrition, and responsive stimulation interventions have been developed to improve child survival, growth and development outcomes in low- and middle-income countries. Nevertheless, research on integrated implementation approaches to deliver and promote uptake of these interventions is needed, particularly in sub-Saharan Africa.

**Methods/design:**

We will conduct a cluster-randomized controlled trial of a supply-side community health worker (CHW) delivered child health, nutrition, and responsive stimulation intervention alone and in combination with a demand-side conditional cash transfer (CCT) intervention to promote antenatal care and child growth monitoring attendance in rural Morogoro region, Tanzania. Twelve village clusters will be randomly assigned to one of the three trial arms: (1) CHW, (2) CHW + CCT, or (3) Control. Mothers (or another primary caregiver) residing in study villages are eligible for trial enrollment if they are currently pregnant or have a child < 1 year of age at the time of enrollment. For the duration of the trial, CHWs will visit households once every 4–6 weeks to deliver the intervention package and CCTs will be provided for documented antenatal care and routine child health and growth monitoring clinic visits. Participants will be followed-up at 9 months (midline) and 18 months (endline) post-randomization. The primary outcomes of the trial are child development assessed by the Bayley Scales of Infant and Toddler Development (BSID-III) and child height-for-age z-score. Secondary outcomes include a range of maternal, child and household outcomes.

**Discussion:**

This trial will provide evidence on the effect of CHWs and conditional cash transfers on child growth and development. The results of the trial may be generalizable to similar settings in sub-Saharan Africa.

**Trial registration:**

ISRCTN10323949, Retrospectively registered on October 3, 2017.

## Background

In 2010, it was estimated that over 300 million children under the age of five were stunted and approximately 250 million children in low- and middle-income countries (LMIC) did not reach their development potential [1, 2]. Suboptimal development during infancy may persist through childhood and lead to poor schooling achievement and human capital outcomes later in life [3, 4]. As a result, alleviating early life adversity and supporting child development may help reach long-term health and poverty reduction goals in LMIC.

Intervention packages that include multiple health, nutrition, and responsive stimulation components may be impactful in promoting children’s growth and development [5]. Further, community-based and integrated strategies may provide greater intervention coverage, impact, and address the limited human and financial resources in LMIC [6]. Community health worker (CHWs) can increase the rate of facility births, uptake of child immunizations, improve breastfeeding practices and reduce morbidity and mortality for newborns; however, the effect of CHW-delivered interventions on child growth outcomes remains unclear [7–9]. Community-based approaches to deliver responsive stimulation interventions have been shown to improve child development outcomes in LMICs [10]. Nevertheless, evidence on the effect of CHW delivered child health, nutrition, and responsive stimulation intervention packages on child growth and development outcomes in sub-Saharan Africa remains sparse.

Conditional cash transfers (CCTs) have shown promise in promoting behavioral changes related to health and education outcomes in LMICs [11]. CCTs tied to health service utilization have generally shown positive effects on antenatal care and well-child clinic attendance; however, evidence on child health, nutrition and development outcomes is mixed and limited in the context of sub-Saharan Africa [11, 12]. A meta-analysis of 17 CCTs programs, with the majority of trials conducted in South America, found no effect on child growth outcomes [13]. Nevertheless, studies in Columbia and Mexico have indicated that integration of CCTs with responsive stimulation and group-based parenting-support interventions can improve child development outcomes [14, 15]. Therefore, the effect of CCTs alone and in combination with integrated child health, nutrition, and stimulation interventions remains unclear.

We present the protocol for a cluster-randomized controlled trial of a supply-side CHW delivered health, nutrition, and responsive stimulation intervention alone and in combination with a demand-side CCT intervention to promote antenatal care and routine child growth monitoring visit attendance in rural Tanzania. The co-primary outcomes of the trial are child development and linear growth. We will also examine a range of secondary maternal, child, and household outcomes. This trial is intended to inform whether policymakers in Tanzania and similar settings should consider adding a responsive stimulation to CHW curriculums and whether coordination of CHW and CCT programs can improve child growth and development.

## Methods / design

We will conduct a proof-of-concept cluster RCT to examine the effect of a supply-side CHW delivered health, nutrition, and responsive stimulation intervention alone and in combination with a demand-side CCT tied to antenatal care and routine child growth monitoring clinic attendance (trial registration: ISRCTN10323949). The trial protocol was developed by collaborators at the Ifakara Health Institute in Tanzania and the Harvard T.H. Chan School of Public Health in the United States. This protocol (version 2.0/17 March 2017) was written in concordance with the Standard Protocol Items: Recommendations for Interventional Trials [16].

The trial flow diagram is presented in Fig. 1. Twelve village clusters in the Ifakara Health and Demographic Surveillance (HDSS) system were randomly assigned to one of the three trial arms: (i) CHW, (ii) CHW + CCT, or (iii) Control. The CHW arm will receive the CHW delivered health, nutrition and responsive stimulation intervention for the duration of the trial. The CHW + CCT arm will receive the same CHW intervention combined with a CCT intervention for the duration of the trial. The control arm will have access to the existing clinic-based health, nutrition and development services; no quality improvement to existing serves will be provided. A total of ~ 600 mother/caregiver-child dyads residing in the study villages will be enrolled. Study participants will be assessed at midline (9 months of follow-up) and endline (18 months of follow-up) for primary and secondary outcomes.

**Fig. 1 Fig1:**
[figure not shown]
Trial flow diagram

### Primary and secondary outcomes

The co-primary outcomes of the trial are (1) child development composite scores and (2) child linear growth as assessed by height/length-for-age z-score (HAZ) at trial endline. We will also assess effect of the interventions on child development and child linear growth at midline as secondary outcomes. Additional secondary outcomes include a range of household, maternal, and child outcomes that may be affected by either the CHW and/or CCTs interventions. Secondary outcomes assessed at midline and endline include: (i) child weight-for-age z-score (WAZ), (ii) child weight-for-height/length z-score (WHZ), (iii) child head circumference-for-age z-score (HCAZ), (iv) child mid-upper arm circumference (MUAC) z-score, (v) antenatal and growth monitoring clinic visit attendance, (vi) child morbidities, (vii) child hospitalization, (viii) maternal depression and anxiety, (ix) maternal social support, (x) women’s empowerment, (xi) caregiver knowledge of child development, (xii) caregiver report on engagement in stimulation activities and (xiii) household food security.

### Trial setting

This trial is being conducted in the Ifakara Health Institute HDSS in the Kilombero and Ulanga districts in the Morogoro region of Tanzania [17]. The site is located between latitudes 8°00′S and 8°35′S and longitude 35°58′E to 36°48′E. The HDSS study area is located approximately 450 km by road from Dar es Salaam with a catchment population of ~ 400,000 people. The study area is predominately rural, and the majority of residents are subsistence farmers. A recent study conducted in the Ifakara HDSS found a 16.9% prevalence of low birthweight (< 2500 g) and a 36.2% stunting prevalence (HAZ < -2) among children 18–36 months of age [18].

### Trial population

Women/caregivers and their infants (if applicable) will be eligible for trial enrollment if they met the following inclusion criteria at the time of the enrollment visit: (1) permanent resident of study village, (2) currently pregnant (self-reported) or have a child < 1 year of age, (3) and provide written consent for enrollment. Women/caregivers will be excluded from participation if they: (1) are currently enrolled in any other clinical trial or intervention study, or (2) do not provide informed consent. Written informed consent will be obtained for all participants.

### Sample size

Sample size calculations were based on randomization of 12 clusters with a cluster size of approximately 50 mother/caregiver-child pairs. We assumed a nominal Type I error rate (alpha) of 0.05 and assume a coefficient of variation of 0.49 an intra-cluster correlations of 0.01. We will have 80% power to detect a standardized mean difference (SMD) of 0.40 standard deviations in normalized anthropometric outcomes (HAZ, WHZ, WAZ), and 0.53 standard deviations of development z-scores. These are quite large effect sizes; however, this is a proof-of-concept trial and there is potential of the intervention package and the combination of CHWs and CCT to provide a sizable impact on child growth and development.

### Randomization and interventions

Village clusters will be allocated in a 1:1:1 ratio to one of the three trials arms: (i) CHW, (ii) CHW + CCT, or (iii) Control. Stratified randomization will be done by a non-study statistician in Boston, USA according to a computer-generated randomization list with sequence blocks of three. Randomization will be stratified by semi-urban (six villages) and rural (six villages) villages to increase the likelihood of baseline balance.

#### CHW delivered child health, nutrition and responsive stimulation intervention

The CHW and CHW + CCT arms will receive the same supply-side CHW intervention. The project will recruit female CHWs living in the study villages catchment area who had completed a one-year government certified CHW program prior to being selected for the intervention. The government CHW curriculum included two semesters that each covered seven topics. The first semesters covered: (1) fundamentals of communication and customer service, (2) infection prevention and control, (3) management of health care facility, (4) computer application, (5) citizenship and gender, (6) management information systems, and (7) basic life support skills. The second semester covered: (1) fundamentals of social work, (2) disease prevention and control, (3) community-based reproductive, maternal and child health services, (4) community-based health promotion, (5) home-based care, (6) basics of entrepreneurship and life skills, and (7) health facility and community disease management. The main infant intervention components of the CHW curriculum include: 1) community-case management of under-5 childhood illness per Integrated Management of Childhood Illness (IMCI); 2) antenatal and postnatal pregnancy, delivery and essential newborn care counseling and danger signs identification; 3) family planning; 4) and emergency and routine referrals to facilities. The CHWs will be assigned to the study villages at the start of the trial. The salary for the CHWs is ~ 600,000 Tanzanian shillings (~$230) per month.

We will train the CHWs to deliver a responsive stimulation intervention that was integrated into the routine CHW home visit program. The responsive stimulation intervention is a Tanzanian and Swahili adapted version of the UNICEF and WHO Care for Development package [19]. The intervention includes communication of essential early childhood development knowledge, promotion of caregivers’ sensitivity and responsiveness, developmentally appropriate play and communication activities, toy making, and problem solving. Caregivers are provided the opportunity to try out responsive stimulation activities with their young child and receive feedback and coaching from the CHW. The CHWs will received a one-week training in September 2017 on the responsive stimulation intervention that included integrated classroom and practical sessions.

CHWs will conduct home visits every 4–6 weeks throughout the trial follow-up period (18 months) to deliver the health, nutrition and responsive stimulation intervention package. The intended duration of the visit is 30–60 min per household, dependent on the health and well-being of the mother and child. One study coordinator will supervise the CHWs throughout the intervention. CHWs will met individually with the study coordinator biweekly to report visit completion. The study coordinator will accompany CHWs at least once per month to supervise home visits and provide feedback on intervention delivery. CHWs will also keep administrative records including the duration of home visits and the composition of messages delivered at each visit that will be reviewed by the study coordinator once a month. Monthly meetings will be held with all CHWs and the study coordinator to discuss progress and troubleshoot emerging challenges. A three-day refresher training on the responsive stimulation intervention will be conducted at trial midline (9 months). We will conduct in-depth qualitative interviews with each CHW at intervention completion to document their experiences and suggestions for improvement.

#### Conditional cash transfer intervention

CHWs will also provide a demand-side CCT intervention to mothers/caregivers in the CHW + CCT arm. The conditions for the cash transfers are documented attendance of antenatal care or routine well-child health and growth monitoring clinic visits. Tanzania currently uses a focused antenatal care model with four visits; one before 16 weeks, at 20–24 weeks, at 28–32 weeks, and at 36 weeks gestation; postnatal child health and growth monitoring clinic visits are recommended to occur monthly until 2 years of age and then quarterly until 5 years [20, 21]. Reproductive and child health cards will be checked at CHW visits to document clinic visit attendance. CHWs will provide the CCTs for the duration of the follow-up period. Pregnant women will receive cash payments of 10,000 Tanzanian Shillings (~ $4.30) per antenatal care visit for up to four total visits. Mothers/caregivers will receive cash payments of 5000 Tanzanian Shillings (~ $2.15) per routine child health and growth monitoring clinic visit for up to one visit per month. Mothers/caregivers signed or provided thumbprints upon receipt of a cash transfer. The study coordinator will conduct random monthly spot-checks to ensure mothers/caregivers received CCTs as documented.

#### Control arm

Villages in the control arm will receive no intervention and have access to existing clinic-based services. No quality improvement activities will be undertaken by the study team.

### Data collection

The schedule of trial enrollment, interventions, and assessments is presented in Fig. 2. Trained fieldworkers will conduct home interviews with mothers/caregivers at baseline, midline (9 months of follow-up) and endline (18 months of follow-up). The fieldworkers will be blinded to the randomized intervention arm. At baseline, all enrolled mothers/caregivers will be administered a standardized questionnaire including demographic and socioeconomic data. Child length/height, weight, head circumference, and MUAC will be taken in triplicate at baseline, midline and endline at the home. Child weight will be measured to the nearest 100 g using a digital scale (Seca, Hamburg, Germany). Length of children < 24 months of age will be measured to the nearest 0.1 cm with a length board (Seca) and height of children ≥24 months will be measured to the nearest 0.1 cm with the use of a portable stadiometer (Seca). Anthropometric z-scores will be calculated using the 2006 WHO child growth standards [22]. At baseline, midline and endline RCH cards will be used to assess antenatal care and child health clinic visit attendance.

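### Clinic attendance is read from the same card that earns cash in the CHW + CCT arm, so contrasts with that arm may mix attendance with better documentation

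*Protocol article*

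**What the plan says.** Under Primary and secondary outcomes, item (v) of the secondary outcomes at midline and endline is "antenatal and growth monitoring clinic visit attendance". Data collection gives its source: "At baseline, midline and endline RCH cards will be used to assess antenatal care and child health clinic visit attendance". No clinic register, facility record or caregiver report of attendance is named. The caregiver recall described under Data collection covers child morbidities and hospitalizations.

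The same card appears in the section Conditional cash transfer intervention. That section states: "The conditions for the cash transfers are documented attendance of antenatal care or routine well-child health and growth monitoring clinic visits". It also states: "Reproductive and child health cards will be checked at CHW visits to document clinic visit attendance". Only one arm is paid: "CHWs will also provide a demand-side CCT intervention to mothers/caregivers in the CHW + CCT arm". The amounts are 10,000 Tanzanian shillings per antenatal visit, for at most four visits, and 5000 shillings per child clinic visit, for at most one a month. CHW home visits take place every 4–6 weeks for 18 months. For the control arm the article says: "Villages in the control arm will receive no intervention and have access to existing clinic-based services".

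**The concern.** Attendance is the behaviour that the cash is meant to change, so it is the first link in any account of how the CCT might affect growth or development. The card records a visit only if the visit was entered and the card can be produced. In CHW + CCT, a missing entry or a lost card costs the caregiver money. In the other two arms it costs nothing. The completeness of the measuring instrument is therefore open to influence by the allocation itself.

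The stated safeguards address other problems:

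- **Fieldworker blinding** protects how a card is read. It does not affect what is written on the card or whether the card survives.
- **The coordinator's monthly spot-checks** confirm that cash reached the caregiver as recorded. They do not confirm that the visit took place.
- **Intention-to-treat analysis, allowance for clustering and adjustment for baseline imbalance** cannot remove a measurement difference that arises after randomization.

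The Discussion remarks that clinic services receive no quality improvement, so CCT effects may be underestimated. If documented attendance rose while the co-primary outcomes did not, a recording difference could be read as more attendance without benefit.

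**Working it through.** The article gives no figure for card completeness or for attendance, so there is no stated figure to reproduce. The calculation shows how large the effect would be under assumed values.

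**Ratio of recorded attendance**

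Recorded attendance = true attendance × probability that an attended visit appears on an available card. If true attendance is equal in the two arms it cancels, and the recorded ratio is the ratio of the two capture probabilities. With 95% assumed in CHW + CCT:

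| Capture in comparison arm (assumed) | Spurious ratio |
|---|---|
| 90% | 0.95 / 0.90 = 1.06 |
| 80% | 0.95 / 0.80 = 1.19 |
| 70% | 0.95 / 0.70 = 1.36 |

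The comparison arm may be control or CHW alone. The article does not say whether CHWs inspect cards in the CHW-only arm. If home visits themselves improve card keeping, the gap between CHW + CCT and CHW is narrower than the gap with control.

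The planned analysis that collapses the two CHW arms is exposed in part. With arms of equal size, and CHW-only capture equal to control, the pooled ratios are:

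- [(0.95 + 0.90)/2] / 0.90 = 1.03
- [(0.95 + 0.80)/2] / 0.80 = 1.09
- [(0.95 + 0.70)/2] / 0.70 = 1.18

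**Chance of a significant result with no true difference (rough guide)**

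Inputs from Sample size and Randomization: 12 clusters allocated 1:1:1, so 4 per arm; about 50 dyads per cluster, so about 200 per arm; intra-cluster correlation 0.01; coefficient of variation 0.49, read as variation in cluster size; alpha 0.05, taken as two-sided.

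- Design effect = 1 + [(0.49² + 1) × 50 − 1] × 0.01 = 1.61
- Effective number per arm = 200 / 1.61 = 124

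Attendance is treated as a binary outcome and two proportions are compared with normal quantiles:

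| Assumed true attendance | 90% vs 95% captured | 80% vs 95% | 70% vs 95% |
|---|---|---|---|
| 50% | 6% | 22% | 52% |
| 70% | 8% | 40% | 80% |
| 90% | 16% | 74% | 99% |

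The nominal level is 5%. These chances depend on applying the article's intra-cluster correlation to attendance, which the article does not claim, and on normal quantiles with only four clusters per arm. The ratios do not depend on either. A modest gap in capture does little harm; a wide one does a great deal. The article gives no way to tell which applies.

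**The case against.** **Sole source.** A reader might infer that the card is the trial's sole source for attendance. The article does not say that. It is condensed, the schedule of assessments is a figure not reproduced in the text, and questionnaire items may be in the full protocol. This stands. The point is confined to the card being the only source named, and to its double role.

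**Bias present.** A reader might also infer that recording does differ by arm, so that the trial will show a CCT effect where none exists. Nothing in the article shows that cards are incomplete, that caregivers influence entries, or that control caregivers lose cards more often. This stands too: the mechanism is plausible, but its occurrence and size are unknown, and every capture percentage above is an assumption.

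**Control cards.** Control cards are not left unread. Fieldworkers use them at baseline, midline and endline like those of the other arms. What control lacks is the payment and the CHW checks between assessments. That narrows the argument but does not remove it, because cash rewards keeping and completing the card in one arm only.

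**Caregiver report.** Caregivers paid for attending may over-report attendance, so the interview answer can err in the same direction as the card. Agreement between the two would then validate nothing. This also stands and limits the use of the second measure.

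**Importance.** Attendance is one of 13 lettered secondary outcomes. The co-primary outcomes are measured directly by blinded staff and do not use the card.

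**Conclusion.** The point holds as a possible bias in one secondary outcome. The named attendance source is also the payment record in one arm, and no stated safeguard covers a difference between arms in card keeping or entry. The CHW + CCT contrasts on attendance, with control and with CHW alone, may therefore combine attendance with documentation. Under the assumed capture rates the spurious ratio is 1.06 to 1.36. These values show the sensitivity of the outcome and do not estimate what occurred.

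The article does not support a conclusion that the attendance result is false, or that the BSID-III and height-for-age results are compromised. A low-cost change to data collection and to the wording of the conclusion is justified; a change to the design is not.

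**What to change.** 1. At each remaining assessment, have the blinded fieldworkers ask every caregiver in all three arms one identical question on the number of clinic visits since the last assessment. They should ask it before requesting the card, and then record whether a card was available.
2. Label the card-based outcome documented attendance, and report card availability by arm beside it.
3. If availability differs by arm, limit the CCT conclusion to documented attendance. Equal availability does not prove that entries are equally complete, so the label should stay in either case.
4. Present the caregiver-reported count as a supportive sensitivity analysis only. Do not make the conclusion depend on its agreement with the card.

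Enrollment began on 14 September 2017, so the first participants reached 9 months around June 2018 and 18 months around March 2019. Follow-up was still ongoing on 16 May 2019. The new items may therefore be possible only for endline visits still to come. For completed rounds, the label and the limit on interpretation still apply, and availability can be tabulated if it was recorded.

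The cost is one or two interview items, one extra table and one sensitivity analysis. The drawback is that caregiver recall is a noisier measure. The intervention is unchanged.
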